## Abstract

**Background:** Placebo has been studied for many years and is ever-present in healthcare. In clinical practice, its use is limited by ethical issues raised by the deception entailed by its administration. **Objective:** To investigate whether, when given detailed information about pain and underlying placebo mechanisms, subjects will have a response similar to that of those subjected to a procedure in which they receive a conventional placebo treatment. **Methods:** The study is designed as a non-inferiority randomized, parallel with a nested crossover trial. In addition, 126 subjects without any known pathology will be included. They will be randomized into two groups. Each subject will undergo three Cold Pressor Tests (CPT): calibration, condition of interest (deceptive placebo or educated placebo), and control. Our main judgment criterion will be the comparison in pain intensity experienced on the visual analog scale between the two CPTs with placebo conditions. **Results:** This study will allow us to rule on the non-inferiority of an “educated” placebo compared to a deceptive placebo in the context of an acute painful stimulation. It is another step towards the understanding of open-label placebo and its use in clinical practice. **Conclusions:** This study has been approved by the ethics committee in France (2017-A01643-50) and registered on ClinicalTrials.gov (NCT03934138).

## 1. Introduction

The placebo effect has been studied for decades and is present in medical and paramedical care. Though placebo treatments have shown their efficacy in numerous pathologies, their use in common practice is limited because of ethical issues. Placebos are utilized mostly as a methodological tool in control groups to demonstrate the efficiency of studied therapies.

Placebo was initially described as an inert substance or therapeutic procedure devoid of any pharmacological effect. Benedetti highlights an important nuance and describes the placebo not only as the inert substance but “its administration within a set of sensory and social stimuli that tell the patient that a beneficial treatment is being given” [1]. Indeed, the placebo effect can be in part defined as a “psychobiological phenomenon occurring in the patient’s brain after the administration of an inert substance, or of a sham physical treatment along with verbal suggestions (or any other cue) of clinical benefit” [2]. Although there is no consensus on the taxonomy of the terms, the placebo effect and the placebo response are not interchangeable terms—the latter being the sum of all non-specific effects taking place after administration of a placebo treatment and the placebo effect being precisely the psychosocial and psychobiological non-specific effects [1,3,4,5]. However, some authors suggest different definitions [6].

Many factors have been identified as potentially influencing the placebo effect and several mechanisms have been studied that elicit it [1,4]. The two main mechanisms implicated are learning and expectations. Other mechanisms such as social learning, memory, concentration, reward, and decreased anxiety [7] have also been studied and can either be classified into learning processes or expectations’ modulation. A third mechanism of keen interest in recent research explores the genetics involved in the placebo effect [8]. Several genes have been identified in the dopaminergic, opioidergic, endocannabinoidergic, and serotoninergic pathways as modulators of a subject’s placebo response.

Throughout recent decades, endogenous placebo mechanisms have been investigated. They refer to endogenous cascades triggered by expectancy, learning, and their combination, whereas exogenous mechanisms depend on pharmacologically induced effects [6]. Levine brought up this hypothesis for the first time in 1978 and since then many studies have confirmed it [9,10]. The authors described an endogenous response triggered by a positive expectancy [11]. Studies using fMRI [12,13] and PEI [14] have shown common mechanisms for placebo-induced and opioid-induced analgesia, particularly the activation of common cerebral regions. These findings have been confirmed and further studied as shown by recent reviews [15,16]. There is now solid evidence identifying the areas of the brain in play during placebo analgesia for example.

The expectation modulation mechanism includes the patient’s expectations and that of the practitioner. A group of subjects hoping for a positive effect of a placebo treatment is more likely to experience the expected improvement of the symptoms [17]. The trial proposed in the present article attempted to modulate the subject’s positive expectations using their understanding of underlying placebo mechanisms.

### 1.1. The Use of Placebo in Contemporary Clinical Practice

Numerous studies have explored the use of placebo treatments in clinical practice in industrialized countries. In the United Kingdom, in 2013, a survey involving interviews with 783 physicians [18] showed that 78% used placebo treatments at least once a week. In addition, they indicated that at least 97% of physicians had used them, most often impure ones (meaning derived from its original use yet inert on the symptom treated [5]), at least once in their careers. Pure placebos such as saline injection were very rarely utilized. In Denmark, the 2003 study by Hrobjartsson and Norup showed that 86% of general practitioners reported using at least one “intervention with no specific effect on the condition to be treated but a possible non-specific effect” in the previous year [19]. The main reason given was to avoid confrontation with the patient. In Tilburt et al.’s. study in 2008 [20], 334 interns and 345 rheumatologists in the United States were interviewed. Results demonstrated that 55% of practitioners used a placebo at least once during the previous year and 46% at least two or three times a month. Again, the majority of prescriptions were for impure placebos. Of these, 70% were antibiotics, which raises issues for the patient and for the community as well. More recently, a review from Linde and collaborators [21] confirmed these results on a large-scale meta-analysis. Firstly, we can see large intervals of responses (from 29 to 97% used placebo treatments at least once in their career) that seem to indicate that the concepts are quite differently defined in each study. Secondly, we can see that placebo treatments are widely used in practice and that these treatments are more often impure than pure.

### 1.2. Ethical Concerns

The ethical issues raised by the deception associated with placebo treatments limit its use. Indeed, “most physicians agree that the placebo effect plays a significant role, but that the use of placebo is often associated with uncertainty regarding the ethical dimensions of whether and how to communicate the use of a placebo to the patient” [22]. In addition, in the field of research, opinions are divided and, in most countries, there are no official regulations.

A first option is the use of placebo as a lure. That is, the inert nature of the given treatment is hidden from the patient in order to provide a placebo effect. Some authors such as Foddy justify lying to or omitting information from the patient because the treatment is administered in the patient’s interest [23]. However, this represents a hindrance to the patient’s autonomy and strengthens the doctor’s paternalistic relationship with the patient. In this context, the patients cannot give informed consent nor can they refuse the treatment.

Moreover, this deceptive use of placebos can harm the therapist–patient relationship when the deception is discovered or revealed. “When a patient finds that a real illness was treated by a fake drug, the doctor–patient relationship will rupture, and may have long-term consequences on the patient’s capacity to trust any medical advice” [24]. However, placebos can be a useful solution when there is no effective treatment available.

Considering previous arguments, in November 2006, the American Medical Association adopted an ethical policy prohibiting the use of placebo associated with deception in clinical practice. Added to that, many authors favor the use of open-label placebo [25] mostly because of the ease in manipulating patients that is underlined by the discovery of physiological mechanisms involved in the therapeutic ritual [4].

### 1.3. Placebos without Deception

However, if the patient takes a placebo treatment with full disclosure in regard to the nature of the treatment, will the therapeutic effect observed in the previously cited studies still be present? This question had started to raise interest as early as 2003. Authors such as Aulas and Rosner conducted a clinical trial on non-blind placebos as treatments for anxiety, in subjects suffering from depression, to answer this question [26]. This trial was a good starting point yet suffered from important methodological limitations. To overcome these limitations, Kaptchuk et al. designed one of the first randomized controlled trials on placebos without deception. This study compared an open-label placebo (OLP) to a no treatment arm with patients suffering from irritable bowel syndrome (IBS) [27]. In the OLP group, patients knew “that the placebo pill was an inactive (i.e., «inert») substance like a sugar pill that contained no medication.” About 15 min were set aside to provide information about placebo. The symptom improvement in this group was clinically and statistically superior to the control condition. Results were surprisingly high: “finally, the percentage of patients reporting adequate relief (59%) is comparable with the responder rates in clinical trials of drugs currently used in IBS,” demonstrating that, in a context of persuasive reasoning, OLP may show effectiveness comparable to the established treatments in IBS.

Other studies have confirmed Kaptchuk’s team’s hypothesis [28]: placebos without deception seem to improve a range of clinical symptoms while maintaining patient autonomy and trust in the physician. Recent reviews found OLP treatments to be clinically effective compared to no-treatment groups [29] on several conditions including: IBS, depression, allergic rhinitis, chronic low back pain, and attention deficit hyperactivity disorder (ADHD).

Nonetheless, it is still unclear how OLPs work [30] and how to increase their effectiveness. One variable that is to be considered is the rationale given during its administration.

Such explanations are starting to be studied more and more. For example, Locher et al. [31] compared OLP and deceptive placebos with a focus on the rationale given to the patients. The research hypothesis was that the educated placebo would still be less effective than the deceptive placebo. Other studies such as Schaefer et al.’s RCT [32] looked at information as a trigger of positive expectancy in allergic rhinitis.

This protocol’s hypothesis is that knowledge and understanding of the mechanisms at work in the placebo effect will increase the intensity of the open placebo response towards a non-inferiority compared with deceptive placebo. This is the reason the group with the variable of interest is called “educated” placebo. This study will be the first, to our knowledge, to test for non-inferiority between an educated placebo and a deceptive one.

## 2. Materials and Methods

### 2.1. Objectives

The main objective of this study is to investigate whether or not an educated placebo is non-inferior to a deceptive placebo treatment on treating acute pain intensity. Secondary objectives of the study include verifying the superiority of both placebo treatments with a no-treatment Cold Pressor Test (CPT). We will also assess the effect of both placebo treatments on anxiety. This study also aims to measure whether or not the educational video was effective in transmitting knowledge about the placebo effect.

### 2.2. Design

We will conduct a non-inferiority randomized, parallel with a nested crossover trial comparing educated open-label placebo to deceptive placebo. This monocentric study will be carried out by two licensed physiotherapists in a University Hospital near the campus.

Written informed consent will be obtained from subjects prior to their participation in the study. The investigation will consist of a single two-hour session. Participants will receive a 20€ participation compensation.

The subjects meeting the inclusion criteria (detailed below) will be randomized into two groups: (1) educated placebo or (2) conventional/deceptive placebo. Each will be subjected first to a calibration CPT, and then, in a randomized order, will receive the CPT under the condition of interest (either the Conventional placebo CPT (CPTp) or the Educated placebo CPT (CPTe)) and a Control CPT (CPTc). This is represented in Figure 1.

Regarding blinding, investigators will not be blind as they deliver the treatment openly in the educated group. Patients in the deceptive placebo group will be blinded. However, patients in the educated placebo group will not be due to the nature of OLP. The analysis will be done blindly as the analyst will not know which group received which treatment.

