### 2.3. Assessment

The primary end point will be the difference in pain intensity, assessed on a 100-point visual analogue scale (VAS), between the educated OLP and the deceptive placebo treatments at the end of the placebo condition CPT. We have chosen pain intensity as opposed to pain threshold because it involves less motivational and cognitive components [33].

The main secondary end point will be, for each subject, the difference in pain intensity, also assessed by VAS, between open or deceptive placebo versus no-treatment control. Secondarily, a questionnaire (inspired by Hughes et al.’s data [34]) measuring knowledge regarding the placebo effect will be completed by all the subjects after the study and also before the educational video for the educated placebo group. In addition, all the subjects will complete another questionnaire about their perception of the investigators and of the study [35]. Blood pressure (BP) and heart rate (HR) values will be obtained before, during, and after each CPT by means of an automatic blood pressure monitor. Finally, subject’s anxiety will be evaluated through heart rate variability. Before the CPT treatment, an expectancy questionnaire will be used [36].

We expect to find a non-inferiority between both groups on the main end point. Considering the nature of the dependent variables and the choice of the painful stimulation, we expect a high interindividual variability. This has been limited as best as possible by the cross-over conducted in both arms of the study.

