### 2.7. Randomization

Randomization was carried out in several steps. Firstly, an analyst from inside the team wrote the code to get a randomized spreadsheet of groups and CPT orders. The rest of the procedure was conducted by the research team’s staff not involved in the protocol. Another analyst was asked to attribute to each group an unidentifiable name in order to blind the analysis of results (group A and group B) as well as choose a random seed. Lastly, another person made individual, numbered, and sealed envelopes with the randomization results inside. This entire process was done with no involvement from the investigators. The envelopes are kept under lock and key.

This process allows for preservation of the blinding of the analyst (not knowing which treatment group A and B received) and maintains the investigator in the dark regarding group attribution until the envelope is opened.

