### 2.10. Part II: Experimental CPTs

During the break between calibration and the second CPT, the subject will receive the information related to the group they are randomized into. For the deceptive placebo group, the video will describe the history of hygiene and correct method for washing hands. For the educated placebo group, the video will be an educational video about placebo, its physiology, and the use of OLP. Movies are similar in terms of duration (~11 min), image quality, and format. After both videos, there will be a time where questions can be answered by the investigators. The educated placebo group will fill out a questionnaire regarding their knowledge of the placebo effect before watching the educational video.

The test phase will be divided into two parts in a random sequence to compensate for habituation effect: deceptive placebo CPT (CPTp) or educated placebo (CPTe) and control CPT (CPTc). For the CPTp and CPTe, two milliliters of the neutral placebo cream are applied beforehand following a standardized procedure: four round-trips on the forearm along its submerged part and on the dorsal and palmar side of the hand and an expectancy questionnaire is filled out. The immersion time (t) in cold water will be that previously calibrated.

While applying the neutral cream, the examiner will explain to the deceptive placebo group, that “it is a cream effective in fighting cold-related pain.” In the Educated placebo condition, the examiner states that it is “a placebo cream, containing no active substance that is effective in fighting cold-related pain. All the mechanisms shown in the previous film will be at work. In a way, your brain will be secreting the active components itself.”

Under the control condition, no cream will be applied.

The examiner will be aware that the same placebo cream is used for the two groups, in order to simulate real situations in which the practitioner administering or prescribing the placebo does so with full knowledge of its presence. The patient will not be blinded in the OLP group and will be blinded in the deceptive placebo group. The analyst will be blinded to group allocation.

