Another choice made for this protocol is the use of VAS as the main evaluation criterion. This measure of pain intensity is not influenced by the cognitive and motivational components that influence pain tolerance or pain threshold or duration of immersion [33]. Its ease of use and of comprehension is another advantage [44]. The numerous secondary criteria will allow to assess the anxiety subjects felt via measure of their heart and respiratory rate. Expectancy and perception of the study and the investigator will be measured with questionnaires. Both groups will fill out a placebo knowledge questionnaire with no prior explanation on the effect. Only the educated placebo group will take this test again once the protocol is finished. This will allow us to control the understanding of the educational video.

The choice of using a cross-over methodology when comparing placebo to no-treatment allows us to control for each subject and each group with a no-treatment measure. This is a methodological strength of the protocol. The randomization of the order in which these control and placebo CPTs are done allows for adjusting on habituation that other studies have found [45]. Each CPT takes place after a 20 min wash-out period where vasodilatation may return to its baseline state. This is verified by a check that hand temperature is comparable on both hands as well as having the VAS return to 0 before performing a new test.

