Lastly, there persists a difficulty in the blinding of the different people involved. To be close to a clinical setting, it is impossible to blind the patient and the therapist. However, an independent assessor could help in blinding the assessment. This was not done in this protocol for material reasons. Instead, the primary outcome is self-reported and the analysis is done blindly by the statistical team.

To address these multiple challenges and avoid discrediting future OLP research, we argue that there is a need to give in-depth explanations of what happens during research protocols that elicit placebo responses whether they are open or not. However, the current scientific publication process often restrains authors towards the number of words used in an article. This is done for obvious reasons, yet does not allow for the exhaustive detail to be given in regard to the protocols and their justifications. This is why it seems crucial to encourage authors to publish their detailed research protocols and methodological considerations either in separate articles or in formats with a less restrained approach to the word limits.

In regard to this protocol, depending on the results, future research will be conducted to investigate the cognitive levers associated with the rationale that can increase OLP effectiveness. Comparisons between an optimized open-label placebo and several treatments in patients affected with persistent pain such as fibromyalgia or low back pain will also be designed and carried out.

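### The blinded-analyst claim cannot cover the whole analysis, because the knowledge questionnaire reveals the educated arm; the primary analysis can still stay masked

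*Protocol article*

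**What the plan says.** **The blinding claim.** Section 2.2 says "The analysis will be done blindly as the analyst will not know which group received which treatment". Section 2.7 gives the mechanism: a second analyst replaces the group names with the labels A and B. Section 2.10 repeats that the analyst is blinded. Section 4.2 explains that no independent assessor was used and that, in place of one, "the primary outcome is self-reported and the analysis is done blindly by the statistical team".

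**The questionnaire.** Section 2.3 says that the placebo-knowledge questionnaire "will be completed by all the subjects after the study and also before the educational video for the educated placebo group". Section 2.10 agrees: "The educated placebo group will fill out a questionnaire regarding their knowledge of the placebo effect before watching the educational video". Section 2.11 has everyone answer at the end, the deceptive group for the first time and the educated group for the second. Section 4.1 says that both groups answer without prior explanation and then: "Only the educated placebo group will take this test again once the protocol is finished".

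**The planned analyses.** Section 2.13 tests non-inferiority with a one-sided 95% confidence bound from a linear regression that adjusts for pain without placebo and for test sequence. It also plans a paired t-test of knowledge before and after the video, in the educated placebo group by name. Section 4.1 adds a check of whether the questionnaire influenced the placebo response.

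**The concern.** Neutral labels hide the arms only if nothing else in the data gives them away. Here a whole variable does, because one label has a repeated questionnaire and the other does not. One planned test can be run in only one arm. The check on questionnaire influence has to join questionnaire records to pain scores.

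This matters because analyst masking is the only blinding that spans both arms. The investigators are not blinded, and neither are the educated-arm subjects. Section 2.13 leaves some decisions that are better taken without knowledge of the arms: what counts as a deviation for the per-protocol set, and how the imputation model is built if 5% to 20% of primary values are missing. Section 2.3 also records that the authors expect to find non-inferiority.

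**Working it through.** **1. Does the questionnaire identify the arm under every account of its timing?**

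| Account | Educated arm | Deceptive arm |
|---|---|---|
| Sections 2.3, 2.10, 2.11 | before the video and at the end | at the end only |
| Section 4.1, read as both groups answering at the outset | at the outset and at the end | at the outset only |

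The Section 4.1 sentences can also be read to agree with the first row. On any reading, only the educated arm has two records per subject. Identification does not depend on knowledge scores being higher after the video, which is something the trial sets out to measure.

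**2. Does the primary analysis need the questionnaire?** No. Under Section 2.13 the model needs the placebo-test VAS, the control-test VAS, the test sequence and the A/B label.

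**3. Does the one-sided test need the arm identity?** Inputs from Section 2.12: margin 10 mm, SD 21.9 mm, alpha 0.05, power 80%, 60 per group.

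- The plan's own figure: n = 2 × (1.645 + 0.842)² × 21.9² / 10² = 59.3, so 60 per group. Then 120 × 1.05 = 126. Both figures reproduce with a one-sided 0.05 test; power at 60 per group is 80.4%.
- Standard error, unadjusted: 21.9 × √(2/60) = 4.00 mm.
- Distance from estimate to one-sided bound: 1.645 × 4.00 = 6.58 mm.
- Non-inferiority is shown if the observed difference, educated minus conventional, is below 10 − 6.58 = 3.42 mm.

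Let d be the observed A−B difference. The two upper bounds are d + 6.58 and −d + 6.58, and both can be computed without the key. If d lies within ±3.42 mm, both are below 10 mm and the conclusion is the same whichever arm is A. With a true difference of zero this has probability 2 × Φ(3.42/4.00) − 1 = 2 × 0.804 − 1 = 0.61. In the other 39% exactly one labelling gives non-inferiority, and the key serves only to read off which applies. Adjustment for control-test pain would reduce the standard error, so these figures are indicative.

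**4. What could selective exclusion do?** The documents give no figure, so the following inputs are assumptions. Removing k of 60 subjects, each x mm above the arm mean, lowers that mean by k × x / (60 − k).

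- k = 1, x = 30: 30/59 = 0.5 mm
- k = 3, x = 21.9 (one SD): 65.7/57 = 1.2 mm
- k = 3, x = 30: 90/57 = 1.6 mm, or 16% of the margin

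These are shifts in a raw arm mean in the per-protocol analysis only. The adjusted estimate would move by a different amount.

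**The case against.** The strongest reply is that this is a condensed article. The order of data release, the point of code-break and the sign-off of analysis sets commonly sit in an analysis plan that is not shown, and nothing in the article prevents a masked primary analysis. That stands, and the absence of those details is not held against the plan. What remains is an affirmative statement made in four sections that the article's own data collection and planned tests contradict. An unseen plan could protect the primary analysis, but it could not make the unqualified sentence true.

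Several stronger readings are tempting and are not supported:

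- A reader might infer that a one-sided test forces the analyst to know the arms. It does not, as step 3 shows.
- A reader might infer that the analyst is unblinded as soon as the data are opened. That assumes that the questionnaires arrive in the same file as the VAS scores, which the article does not say.
- A reader might infer that analyst masking is the whole substitute for a blinded assessor. Section 4.2 also relies on the outcome being self-reported, which does not depend on masking.
- A reader might take the 1.6 mm as an expected bias. It presumes deliberate, one-directional exclusion of subjects about 1.4 SD (30/21.9) above the mean.

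It is also fair that Section 2.13 fixes a good deal: the regression covariates, the missing-data thresholds, a per-protocol rule that excludes on any deviation, and an intention-to-treat analysis that such exclusions cannot move, with caution promised if the two disagree.

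**Conclusion.** The point holds in a limited form. The claim that the analyst will not know the allocation is wrong for the analysis as a whole, because the questionnaire data decode A and B and one planned test names the arm. It can be true of the primary analysis, including the one-sided test, provided that the questionnaire data are kept out until that analysis is finished.

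The consequence is modest. Sample size, power, margin and test are untouched. What is exposed is the independence of the per-protocol and imputation decisions. The size of any resulting shift cannot be derived from the documents: the 0.5 to 1.6 mm range rests entirely on assumed numbers and positions of excluded subjects. The conclusion that the arm can be identified rests on no numerical assumption and survives either account of questionnaire timing.

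**What to change.** - In Sections 2.7 and 2.13, state a two-stage release. Stage one holds subject number, A/B label, test sequence, calibration data, VAS scores and deviations described without arm-revealing text. On these data the analyst fixes the per-protocol set and the imputation model, runs the intention-to-treat and per-protocol analyses, and reports both the A−B and the B−A bound. After sign-off the code is broken, and stage two releases the questionnaires for the paired test and the check on questionnaire influence.
- In Sections 2.2, 2.7, 2.10 and 4.2, limit the blinding claim to stage one.
- Reword the Section 4.1 account of questionnaire timing so that it plainly matches Sections 2.3, 2.10 and 2.11.

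The cost is one data-release step and some wording. No extra staff, subjects or measurements are needed.
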